## **2.5 Sample size**

To assess the cumulative incidence after 10 months of follow-up in residential care centers in Belgium a sample of 381 participants (residents & staff) is required to estimate a proportion of 0.5 with a half-width of 5%, using a 95% Wilson score CI. As residents/staff are clustered within care facilities, the sample size will be augmented by the design effect. Assuming, 15 participants (7 residents and 8 staff) per institution after 10 months of follow-up, and an ICC of 0.12, the design effect is  $2.68 = (1 + 0.12 \times (15 - 1))$ . The total sample size required is  $1022 = 381 \times 2.68$ . At least 69 institutions, each including 15 participants, need to be included in this study, which brings the total sample size to 1035 after 10 months follow-up. In order to obtain at least 15 participants, in 69 institutions after 10 months of follow-up, assuming a drop-out rate of 0.2 and 0.4 for staff (changes in staff, sick leave and holidays) and residents (deceased, hospitalized or transferred residents), would require 22 sero-negative participants per care facility, (10 staff, 12 residents) in all 69 institutions. Assuming a seroprevalence rate of 0.5 at the baseline moment of the study would require 44 participants per care facility, (20 staff, 24 residents) in all 69 institutions.

A final sample size calculation will be performed to check whether the sample size obtained for the second research question will be sufficient for the analysis of the first research question.

To assess the seroprevalence in residential care centers in Belgium a sample of 381 participants (residents & staff) is required to estimate a seroprevalence of 0.5 with a half-width of 5%, using a 95% Wilson score CI.

As residents/staff are clustered within care facilities, the sample size will be augmented by the design effect. Based on the previous calculation, 44 participants (24 residents and 20 staff) will be sampled per institution. Assuming an ICC of 0.12, the design effect is  $6.16 = (1 + 0.12 \times (44 - 1))$ . The total sample size required is  $2347 = 381 \times 6.16$ . At least 54 institutions, each including 44 participants, need to be included in this study, which brings the total sample size to 2376 participants.

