## **2.7 Data Collection**

### **2.7.1 Collection of capillary blood samples and point-of-care test procedures**

The capillary blood samples will be obtained using a lancet to finger prick the middle finger and collect a 1-10 drops of capillary blood. A capillary blood drop will be transferred to the

specimen well of a point-of-care (POC) test (COVID-19 IgG/IgM Rapid Test Cassette, Orient Gene Biotech Co.) using a plastic dropper (delivered with COVID-19 IgG/IgM Rapid Test kit). Two drops (ca. 80 µl) of Orient Gene Biotech sample buffer will be immediately added to the buffer well, with avoidance of air bubbles. If the red colour does not move across the test window or if blood is still present in the specimen well after two minutes, one additional drop of sample buffer should be added into the buffer well. The result should be read in 10 minutes, positive test results may be visible as soon as 2 minutes. The result cannot be interpreted after 15 minutes.

The results of the COVID-19 IgG/IgM Rapid Test Cassette should be interpreted as following:

- **Negative:** The coloured line in the control region (C) changes from blue to red. No line appears in the test line region M or G.
- **Anti-COVID-19 IgM positive:** The coloured line in the control region (C) changes from blue to red and a line appears in the test line M.
- **Anti-COVID-19 IgG positive:** The coloured line in the control region (C) changes from blue to red and a line appears in the test line G.
- **Anti-COVID-19 IgG and IgM positive:** The coloured line in the control region (C) changes from blue to red and a line appears in the test line G and M.
- **Invalid test:** Control line is still completely or partially blue and fails to completely change from blue to red. Insufficient specimen sample or incorrect procedural techniques are the most likely reasons for control line failure. The test should be repeated using a new cassette.

For the study any positive result of IgM or IgG will be considered as a positive result. In case of an invalid test, the test is repeated. When it is still invalid it will be noted as such. Additionally, a few drops of capillary blood will be collected on Dried Blood Spot (DBS) collection cards for (semi-)quantitative analysis of vaccine-induced/infection-induced anti-SARS-CoV-2- specific antibodies as a part of the sub-study performed by Ghent University (details are provided in appendix 6.4).

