### **Secondary objectives**

4. To assess the seroprevalence according to vaccination status among NH residents and staff in Belgium at month 0 and at every follow-up visit in the cohort at month 2, 4, 6, 8 and 10.

The seroprevalence among NH residents and staff in Belgium at month 0, and follow-up in the cohort at month 2 (and if relevant at month 4, 6, 8, and 10), will be reported according to the vaccination status (Number of shots: 0, 1 or 2) and for the subgroups ‘with’ and ‘without’ a history of self-reported SARS-CoV-2 infection, averaged over NHs based on a GEE analysis with exchangeable covariance structure.

5. To assess the risk of getting a SARS-CoV-2 infection since vaccination between:
  - Residents and staff
  - Seropositive and seronegative participants at all timepoints
  - Individuals with or without previous self-reported SARS-CoV-2 infections
  - Adjusted for the updated vaccination degree of NH at all timepoints

For vaccinated participants only, a survival analysis will be performed to investigate the time (in days) to a SARS-CoV-2 infection since vaccination between sero-positive and -negative

participants at all time points. A participant is considered to have an event when the participant had a positive PCR test result (or a positive antigen rapid test, or a positive CT scan, or a positive saliva test in absence of a PCR test). The survival or censoring time (in days) is registered since 14 days after being fully vaccinated (full dose regimen) until first event (or censoring moment). If the proportional hazard assumption holds, a stratified (by NH) Cox proportional hazards regression model will be used to model the hazard of SARS-CoV-2 infection between sero-positive and -negative participants at all time points (modelled by the inclusion of a time-varying seropositivity status), adjusted for type of participant, history of self-reported SARS-COV-2 infections, and a time-varying NH vaccination degree. The analysis will be performed stratified by type of participant or other variables, if the proportional hazard assumption does not hold.

6. To assess the proportion of confirmed COVID-19 deaths and non-COVID-19 related deaths since vaccination and the time until death (within the study timeframe) between sero-positive and -negative participants for NH residents

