For vaccinated NH residents only, a survival analysis will be performed to investigate the proportion of deaths within the study follow-up and the time (in days) to a confirmed COVID-19 death since 14 days after being fully vaccinated (full dose regimen). The survival or censoring time (in days) is registered since 14 days after being fully vaccinated until first event (or censoring moment). A non-COVID-19 related death will be considered as a competing risk in the analysis. If the proportional hazard assumption holds, a stratified (by NH) Cox proportional hazards regression model will be used to model the cause-specific hazards between seropositive and seronegative residents. The latter will be included as a time-varying covariate. A history of self-reported SARS-COV-2 infections, a time-varying NH vaccination degree, province, age, gender, care profile, and presence of COVID-specific comorbidities will be

considered for model adjustment.

7. To assess the duration of SARS-CoV-2 specific antibody response (seroreversion/no antibody response) since 14 days after being fully vaccinated among NH residents and staff in Belgium.

The duration of SARS-CoV-2 specific antibody responses among NH residents and staff in Belgium will be modelled by means of an interval-censored survival analysis. Seroreversion will be defined as a negative rapid test result after at least one positive rapid test result or as two succeeding negative test results (implying the participant did not seroconvert after vaccination within two to four months). The time interval to seroreversion/no response is the time interval between 14 days after the (second) vaccination date (full dose regimen) and the first test moment of a negative test result after at least one positive rapid test or of the two succeeding negative rapid test results. As a sensitivity analysis, the event will also be defined as two succeeding negative rapid test results (whether or not after at least one positive rapid test result), if the rapid test result would turn out to be unstable.

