### **4.3 Bias and limitations**

- Loss of follow-up or missing data is possible, for instance, when a NH staff-member is not present at the moment of sample collection or a sample was not collected due to heavy workload. In this case, effort will be made to contact the NH and collect the sample within two days after the sampling day. In case of, for instance hospitalization of NH resident or self-isolation of NH staff, missing test result data is inevitable. In order to prevent missing data in the online questionnaires, results will be monitored and effort will be made to remind participants to fill in the survey (by e-mail/telephonic contact or at the moment of testing).

- Underestimation of the presence of SARS-CoV-19 seroprevalence among this population due to:

- Testing method limitations, however, the COVID-19 IgG/IgM Rapid Test Cassette (Orient Gene Biotech Co.) provides good sensitivity (92,9%) and specificity (96,3%) (Sciensano, 2020).
- Data collection, however, researchers/CRC's in charge of collecting the samples will be trained to ensure correct use of the COVID-19 IgG/IgM Rapid Test Cassette and interpretation of the results to minimize reporting bias.

- Due to practical limitations, seroprevalence data cannot be collected at the same point in time in all participants in this study. Seroprevalence, however, is subjected to fluctuations of the infection rate in the current SARS-CoV-2 pandemic and is therefore also time-dependent. Therefore, the maximal difference between the first and last samples collected within the baseline collection round is set at  $\pm 4$  weeks days.

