#### **6.4.3. Study design**

This sub-study follows the same time scheduling as the seroprevalence study. For each participant, in addition to every POC rapid antibody test, a few drops of capillary blood will be collected on a Dry Blood Spot saver card (4 saturated spots).

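### Objectives 5 and 6 rest the serostatus exposure on one rapid-test reading per visit and state no handling of test error, although objectives 7 and 10 do

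*Protocol*

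**What the plan says.** Section 3.2 of the protocol numbers these as objectives 5 and 6; they are secondary objectives 2 and 3 in section 2.1.

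- **Objective 5 (infection).** "For vaccinated participants only, a survival analysis will be performed to investigate the time (in days) to a SARS-CoV-2 infection since vaccination". The model is a Cox regression stratified by nursing home. Serostatus is "modelled by the inclusion of a time-varying seropositivity status", with adjustment for type of participant, self-reported earlier infection and the home's vaccination degree over time.
- **Objective 6 (COVID-19 death, vaccinated residents).** Cause-specific hazards are compared between seropositive and seronegative residents. On serostatus: "The latter will be included as a time-varying covariate".
- **What counts as seropositive.** The text of these two objectives names no assay. Section 2.7.1 settles it for the whole study: "For the study any positive result of IgM or IgG will be considered as a positive result". The cassette is repeated only when invalid.
- **Accuracy.** Section 4.3 gives sensitivity 92.9% and specificity 96.3%. It discusses test limitations only as a cause of underestimated seroprevalence.
- **Other objectives.** Objective 7 adds a sensitivity analysis requiring two negatives in a row "if the rapid test result would turn out to be unstable", and objective 10 has a similar one. Objectives 5 and 6 have nothing of the kind.
- **A second antibody measurement.** Section 6.4.3 states that, "in addition to every POC rapid antibody test, a few drops of capillary blood will be collected on a Dry Blood Spot saver card". Section 6.4.4 plans an ELISA for anti-S1 and anti-NCP antibodies on these spots. Neither section links the result to objectives 5 and 6.

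**The concern.** The same cassette readings define the event in objectives 7 and 10 and the exposure in objectives 5 and 6. The protocol foresees unstable readings in the first use but not in the second.

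The second use is the more sensitive one if most fully vaccinated people are truly seropositive. A small false-negative rate applied to a large truly positive group yields many false negatives. They fall into a small seronegative group, which is one side of the hazard ratio. If those people are as protected as other seropositive people, the hazard ratio moves toward 1, and weak separation by the test may be read as weak protection by antibodies. The serostatus contrast is one of the comparisons named in objective 5 and the central one in objective 6.

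**Working it through.** **The plan's own figures.** The protocol gives no number for these Cox models. Its sample size is a precision calculation for a proportion. It reproduces (381 × 2.68 gives 1022; 381 × 6.16 gives 2347; 69 × 44 = 3036) but does not bear on this point.

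**Inputs**
- Sensitivity Se = 0.929 and specificity Sp = 0.963 (section 4.3).
- True seropositive share p after full vaccination: not in the protocol. Assumed 0.80, 0.90 and 0.95, with 0.50 and 0.98 as outer values. The only planning value, in section 2.5, reads "Assuming a seroprevalence rate of 0.5 at the baseline moment of the study" and refers to the whole sample at baseline, not to vaccinated people.
- True hazard ratio, seropositive against seronegative: 0.30 and 0.50, for illustration.

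**Step 1: false share of negative readings**

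f = p(1 − Se) / [p(1 − Se) + (1 − p)Sp]

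- p = 0.80: 0.0568 / (0.0568 + 0.1926) = 0.228
- p = 0.90: 0.0639 / (0.0639 + 0.0963) = 0.399
- p = 0.95: 0.06745 / (0.06745 + 0.04815) = 0.583

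**Step 2: false share of positive readings**

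g = (1 − p)(1 − Sp) / [(1 − p)(1 − Sp) + p·Se]

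This is 0.0099, 0.0044 and 0.0021 for the same p, so almost all contamination is on the negative side.

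**Step 3: apparent hazard ratio**, with errors independent of infection risk

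HR_obs = [(1 − g)HR + g] / [(1 − f) + f·HR]

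For p = 0.95 and HR = 0.30: numerator 0.9979 × 0.30 + 0.0021 = 0.3015; denominator 0.4165 + 0.5835 × 0.30 = 0.5916; ratio 0.51.

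| Assumed p | False share of negatives | True 0.30 appears as | True 0.50 appears as |
|---|---|---|---|
| 0.50 | 6.9% | 0.34 | 0.54 |
| 0.80 | 22.8% | 0.37 | 0.57 |
| 0.90 | 39.9% | 0.42 | 0.63 |
| 0.95 | 58.3% | 0.51 | 0.71 |
| 0.98 | 78.3% | 0.67 | 0.82 |

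**Step 4: dependence on sensitivity.** For p from 0.80 to 0.95, the false share of negatives is 11–37% if Se is 0.97, 23–58% at 0.929, and 38–75% if Se is 0.85.

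**Step 5: dependence on who the false negatives are.** Suppose the false negatives have so little antibody that their hazard equals that of true negatives. The denominator in step 3 is then 1, and only the numerator dilutes the contrast. An HR of 0.30 for the remaining seropositive people would appear as 0.307, 0.303 and 0.301 at p = 0.80, 0.90 and 0.95. Step 3 and this case bracket the plausible attenuation.

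Step 3 is a ratio of mean hazards. It ignores stratification by home, covariate adjustment and change of serostatus over time, so it shows direction and rough size only.

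**The case against.** **The main figures rest on an assumption.** No part of the protocol gives seropositivity after vaccination, and at the one planning value of 0.5 the effect is small. This stands, and a reader should not take 23–58% as a property of this cohort. Still, 0.5 is a baseline figure from a study designed before vaccines were available. Objective 7 treats two negatives after vaccination as failure to respond, which implies that a positive result is expected.

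**The accuracy figures may not apply.** Section 4.3 cites a 2020 source and does not say which population was tested; vaccination in Belgian nursing homes began in January 2021. This also stands, and is why step 4 shows a range.

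**Error handling may sit in a statistical analysis plan that is not shown.** That is possible, and the absence of a correction method alone would be no finding. But section 3.2 fixes the exposure, time origin, stratification and covariates, and provides for unstable tests in two objectives and not in these two. That unevenness is in the protocol itself.

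**Risk by rapid-test result is a coherent question.** It is, and participants receive that result. This is a reason to keep the rapid-test model.

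**Stronger readings the documents do not support**
- That readings are declared error-free and carried forward to the next visit: no such rule is stated.
- That the ELISA should replace the rapid test as main exposure: the protocol gives no accuracy for the ELISA on dried blood spots, and it belongs to a sub-study with its own objective.
- That requiring two negatives in a row solves the problem here. With independent errors it would cut the false share at p = 0.95 to 0.95 × 0.071² / (0.95 × 0.071² + 0.05 × 0.963²) = 9.4%. But visits are 60 days apart, so as an exposure rule it delays classification. It also makes classification depend on surviving uninfected to the next test.

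**Conclusion.** The point holds in conditional form. The exposure in objectives 5 and 6 is one rapid-test reading per visit, and no handling of its error is stated, although the protocol provides for it elsewhere. With the protocol's accuracy figures and an assumed 80–95% true seropositivity, about 23–58% of negative readings would be false, and a true hazard ratio of 0.30 would appear as about 0.37 to 0.51. This rests on three things the protocol does not establish: the seropositive share after vaccination, the validity of the accuracy figures for vaccine-induced antibody, and errors unrelated to infection risk. If false negatives are mainly people with low antibody levels, the attenuation is smaller.

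A reader might infer that the study will find no protection by antibodies. The figures do not show that: at 95% seropositivity a true 0.30 still appears as roughly half the hazard. The risk is an understated association and an over-read result when the estimate is close to 1.

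**What to change.** Keep the rapid-test Cox models as planned. Pre-specify for objectives 5 and 6:

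1. A sensitivity analysis with serostatus taken from the anti-S1 ELISA on the dried blood spot collected at the same visit.
2. The rapid-test hazard ratio corrected for misclassification, for example by MC-SIMEX, over a stated range of sensitivity and specificity (sensitivity 0.85 to 0.97 would cover the values examined here).
3. A statement that a hazard ratio near 1 will be interpreted in the light of both.

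Do not carry objective 7's two-negative rule over as an exposure definition, for the reason given above.

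Cost: extra analysis work, and a wait for the ELISA results, which section 6.4.4 describes as planned. The ELISA has its own error, which the protocol does not quantify, so the first analysis is a check and not a gold standard.

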for COVID-19 relevant preconditions: cardiovascular diseases, diabetes, hypertension, serious heart, lung or renal diseases, immunosuppressing conditions or medication and any form of active cancer. Furthermore, participants (staff and residents) will be asked if they received a COVID-19 vaccination (date, type of vaccine, number of doses), underwent a PCR-/ antigen-test, the date of this test and the result (if more than one test was performed, the date of the first positive test has to be given) or if COVID-19 was confirmed by a CT-scan, and, if they experienced COVID-19 symptoms and when (date). The COVID-19 symptoms episode will be defined according to the Sciensano case definition:

- At least one of following acute principal symptoms not explained by another clear cause: coughing, dyspnoea, chest pain, sudden loss of olfactory sense and/or taste;

OR

- At least two of following symptoms not explained by another clear cause: fever, myalgia, tiredness, rhinitis symptoms, sore throat, head ache, anorexia, diarrhoea, acute confusion, sudden collapse

OR

- Worsening of chronic respiratory symptoms (COPD, asthma, chronic cough) not explained by another clear cause

Additionally, staff members are asked questions concerning vaccine hesitancy (if and why they hesitated to get vaccinated against COVID-19), see Appendix 6.3.

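### The objective 5 infection model omits age, sex and comorbidity, which are collected for everyone, so within-home confounding may remain in the serostatus hazard ratio

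*Protocol*

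**What the plan says.** Protocol 3.2, secondary objectives, item 5 (the second secondary objective in 2.1) defines the population and outcome: "For vaccinated participants only, a survival analysis will be performed to investigate the time (in days) to a SARS-CoV-2 infection since vaccination". The method is that "a stratified (by NH) Cox proportional hazards regression model will be used to model the hazard of SARS-CoV-2 infection", with serostatus "modelled by the inclusion of a time-varying seropositivity status". The model is "adjusted for type of participant, history of self-reported SARS-COV-2 infections, and a time-varying NH vaccination degree". One further sentence covers a failed model assumption: "The analysis will be performed stratified by type of participant or other variables, if the proportional hazard assumption does not hold".

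Item 6 uses the same time-varying serostatus in vaccinated residents, with COVID-19 death as the outcome. Besides prior infection and the home's vaccination degree, it names "province, age, gender, care profile, and presence of COVID-specific comorbidities" as candidates for adjustment.

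Section 2.7.2 lists the preconditions asked of both staff and residents, including "immunosuppressing conditions or medication and any form of active cancer". The baseline questionnaires in Appendix 6.3 ask age, sex and these conditions of staff and residents alike. Care category is on the resident form only.

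**The concern.** Whether a vaccinee tests antibody-positive depends on the host. Age, immune status and comorbidity can plausibly affect the antibody response, and they can also affect the chance of becoming infected or of having an infection detected. A factor related to both will shift the seropositive/seronegative hazard ratio unless the model accounts for it.

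The objective 5 model names three adjusters, and none describes the individual's age or health apart from the resident/staff distinction and prior infection. At stake is how the hazard ratio is read: a value below 1 could reflect antibody-related protection, the health of those who fail to respond, or both, and the planned model cannot separate them. A value near 1 could equally hide a real association if the bias runs the other way.

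**Working it through.** The protocol gives no effect size, event count or power for objective 5, so there is no figure to reproduce. The check has two parts.

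**1. Which differences the planned model already removes**

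- Stratification by nursing home removes differences between homes.
- The participant-type term removes the average resident/staff difference.
- The prior-infection and vaccination-degree terms cover those two factors.
- Stratification by other, unnamed variables is triggered only if proportional hazards fails. It is not a control for confounding.
- Differences in age, sex and comorbidity among residents of one home, or among staff of one home, remain.

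**2. How large the remaining effect could be**

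All inputs here are assumptions; the protocol supplies none of them. Frailty stands for comorbidity or immunosuppression, and the true serostatus hazard ratio is set to 1.

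(a) Rare-event formula. Let p_pos and p_neg be the prevalence of frailty in seropositives and seronegatives, and h the hazard ratio of frailty for infection:

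apparent HR = [1 + p_pos(h − 1)] / [1 + p_neg(h − 1)]

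Example: p_neg = 0.40, p_pos = 0.30, h = 2 gives 1.30 / 1.40 = 0.93.

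| p_neg | p_pos | h = 0.7 | h = 1.5 | h = 2 | h = 3 |
|---|---|---|---|---|---|
| 0.40 | 0.30 | 1.03 | 0.96 | 0.93 | 0.89 |
| 0.50 | 0.30 | 1.07 | 0.92 | 0.87 | 0.80 |
| 0.60 | 0.30 | 1.11 | 0.88 | 0.81 | 0.73 |
| 0.60 | 0.20 | 1.15 | 0.85 | 0.75 | 0.64 |

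If p_neg = p_pos, or if h = 1, the apparent HR is 1.00 and there is no bias. The formula ignores home and participant type, so it is a guide only.

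(b) Simulation of the design. The layout follows section 2.5: 69 homes with 24 residents and 20 staff each. A Cox model stratified by home and adjusted for participant type was fitted with and without a frailty term, 60 runs per scenario. Assumed frailty prevalence was 60% in residents and 20% in staff.

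| Seronegative: frail / not frail | h | HR without frailty term | HR with frailty term |
|---|---|---|---|
| 20% / 10% | 1.5 | 0.94 | 1.00 |
| 30% / 10% | 2 | 0.85 | 1.02 |
| 40% / 10% | 3 | 0.71 | 1.01 |
| 30% / 10% | 0.7 | 1.06 | 0.96 |
| 30% / 10% | 1 | 0.99 | 0.98 |

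The last column lies within simulation error of 1 throughout. Home stratification and participant type therefore do not remove the shift, and a frailty term does. The simulation held serostatus fixed over time and left out prior infection and vaccination degree, so it shows the mechanism and does not predict the result.

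**The case against.** **Covariate detail may belong in a separate analysis plan.** That plan is not shown and may add terms. But the protocol does not defer this choice: it states the model and its adjusters, so the list can be reviewed as it stands.

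**The question may be descriptive.** The objective asks about risk between groups and does not claim that antibodies cause protection. A lightly adjusted hazard ratio can answer whether seronegative vaccinees are at higher risk. This has some force, and it is why the hazard ratio should be reported both ways. It does not justify the present list, which already goes beyond a crude comparison and stops short of obvious host factors.

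**Objective 6 is not a true parallel.** A reader might infer that the two objectives contradict each other. They do not: objective 6 concerns death, covers residents only, and merely considers its list. What stands is that the protocol recognises these variables as relevant to the same exposure and gives no reason for leaving them out of objective 5.

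**Not every candidate is available for everyone at baseline.** Care category is asked of residents only. Vaccine type may be recorded at follow-up for those vaccinated later; because vaccination was organised by home, stratification probably absorbs part of its variation. The case therefore rests on age, sex and comorbidity.

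**Conclusion.** The point holds as a cheap improvement to a secondary analysis. The objective 5 model leaves out individual factors that the study collects for all participants, and neither the strata nor the terms already in the model deal with differences within a home and within participant type.

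A reader might go further and conclude that the hazard ratio will show spurious antibody protection. The documents do not support that. They give no association of frailty with serostatus or with infection, so both size and direction are open. Under the assumed inputs the apparent hazard ratio ran from about 0.7 to 0.96 when frailty raised infection hazard, with 0.64 at the extreme of the formula. It was 1.03 to 1.15 by formula, and 1.06 in simulation, when frail participants had a lower hazard of infection or detection (h = 0.7). It was 1 when frailty was unrelated to serostatus or to infection. Bias in either direction is a reason to adjust.

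The primary seroprevalence and sero-incidence estimates are not touched.

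**What to change.** In item 5 of section 3.2, add age, sex and presence of COVID-specific comorbidities, stated to include immunosuppression, to the Cox model. Use care category for residents, for example in an analysis run separately by participant type. Report the serostatus hazard ratio with and without these terms, so that both the descriptive and the adjusted reading are available.

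If breakthrough infections are few, state in advance a reduced set (age and comorbidity) or penalised estimation. A single propensity score for seropositivity is not a suitable shortcut: serostatus changes over time in this model, and one baseline score does not handle that. The propensity methods planned for the tertiary objectives concern vaccination, a different exposure.

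The cost is a sentence or two of model wording. The variables are already on the questionnaires. The downside is somewhat wider intervals if infections are few.

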#### **Secondary objectives**

1. To assess the seroprevalence according to vaccination status among NH residents and staff in Belgium at month 0 and at every follow-up visit in the cohort at month 2, 4, 6, 8 and 10.
2. To assess the risk of getting a SARS-CoV-2 infection since vaccination between:
  - Residents and staff
  - Seropositive and seronegative participants at all timepoints
  - Individuals with or without previous self-reported SARS-CoV-2 infections
  - Adjusted for the updated vaccination degree of NH at all timepoints
3. To assess the proportion of confirmed COVID-19 deaths and non-COVID-19 related deaths and the time until death since vaccination (within the study timeframe) between sero-positive and -negative participants for NH residents
4. To assess the duration of SARS-CoV-2 specific antibody responses (seroreversion/no antibody response) since vaccination among NH residents and staff in Belgium.

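### Objective 5 names three infection contrasts but specifies one model conditioned on post-vaccination serostatus, so its resident-staff and prior-infection coefficients are not the overall hazard ratios

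*Protocol*

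**What the plan says.** The second of the secondary objectives in section 2.1, repeated as objective 5 in section 3.2, opens with "To assess the risk of getting a SARS-CoV-2 infection since vaccination between" and then lists its comparisons. The first is between residents and staff, the second is "Seropositive and seronegative participants at all timepoints", and the third is "Individuals with or without previous self-reported SARS-CoV-2 infections". The fourth item, the vaccination degree of the nursing home, is marked as an adjustment and not as a comparison.

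The analysis text under objective 5 is limited to vaccinated participants, with time counted from 14 days after full vaccination. If proportional hazards hold, "a stratified (by NH) Cox proportional hazards regression model will be used to model the hazard of SARS-CoV-2 infection between sero-positive and -negative" participants, with serostatus "modelled by the inclusion of a time-varying seropositivity status". Participant type and infection history enter that same model only as covariates: "adjusted for type of participant, history of self-reported SARS-COV-2 infections, and a time-varying NH vaccination degree". No other model is given under this objective. The fallback reads: "The analysis will be performed stratified by type of participant or other variables, if the proportional hazard assumption does not hold".

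**The concern.** The objective puts three contrasts on an equal footing, but the analysis text is written for one of them. For the serostatus contrast, adjusting for type and infection history is sound. The difficulty lies with the other two. Participant type and earlier infection are settled before follow-up starts, whereas serostatus is read at visits after vaccination and can change.

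The protocol itself supports serostatus as an intermediate variable. It makes seroreversion or non-response after vaccination an objective in its own right (objective 7), and section 5.2 describes antibodies as possibly protective against new infection. If residents lose antibodies faster than staff, or if earlier infection sustains them, part of the difference in infection hazard runs through serostatus, and a model that holds serostatus fixed takes that part out. A reader who then took the type and history coefficients as the answers to the first and third comparisons would be looking at a different quantity from the one the objective describes.

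**Working it through.** **No figure to reproduce.** The protocol gives no hazard ratio, event count or precision for objective 5. The check is therefore of the mechanism, on assumed inputs.

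**From the protocol:** 24 residents and 20 staff per home (section 2.4); visits about 60 days apart up to day 300 (section 2.4); rapid-test sensitivity 92.9% and specificity 96.3% (section 4.3).

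**Assumed, not in the documents:** hazard ratio for seropositivity h = 0.3 (also 0.5); everyone seropositive at the start; probability of seroreversion per interval 0.20 in residents and 0.05 in staff (also 0.06 and 0.05), and 0.03 with and 0.15 without prior infection; baseline hazard 0.0015 per day; a direct effect d that bypasses serostatus, varied as shown below.

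**What each model estimates.** Let the hazard be baseline × h (if seropositive) × d (if resident). With pR and pS the seropositive shares of residents and staff:

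- model with accurate serostatus: resident-staff ratio = d
- model without serostatus: ratio = d × [1 − pR(1 − h)] / [1 − pS(1 − h)]

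The two agree only if pR = pS or h = 1.

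**Hand check, d = 1, h = 0.3 (ignoring removal of those already infected).**

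- Residents vs staff, first interval: (1 − 0.7 × 0.80)/(1 − 0.7 × 0.95) = 0.440/0.335 = 1.31
- Residents vs staff, fifth interval: pR = 0.80^5 = 0.328, pS = 0.95^5 = 0.774; 0.771/0.458 = 1.68
- Prior infection vs none, first interval: (1 − 0.7 × 0.97)/(1 − 0.7 × 0.85) = 0.321/0.405 = 0.79
- Prior infection vs none, fifth interval: 0.97^5 = 0.859, 0.85^5 = 0.444; 0.399/0.689 = 0.58

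**Simulation.** 400,000 participants, five 60-day intervals, serostatus updated at each interval. The fit was a piecewise-exponential Poisson model, the analogue of Cox regression with a time-varying covariate. Nursing-home strata were not simulated, and the prior-infection runs used the same 24:20 split.

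| Scenario | Without serostatus | With serostatus, error-free | With serostatus, protocol's test accuracy |
|---|---|---|---|
| Resident-staff, all through serostatus, h = 0.3 | 1.56 | 1.01 | 1.15 |
| Same, h = 0.5 | 1.28 | 1.00 | 1.09 |
| Direct effect 1.3 as well, h = 0.3 | 1.99 | 1.30 | 1.50 |
| Direct effect 0.7, h = 0.3 | 1.09 | 0.70 | 0.81 |
| Seroreversion 0.06 vs 0.05, direct 1.3, h = 0.3 | 1.35 | 1.31 | 1.31 |
| Prior infection, all through serostatus, h = 0.3 | 0.65 | 1.00 | 0.86 |
| Prior infection, direct 0.6, h = 0.3 | 0.40 | 0.60 | 0.52 |

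The simulated 1.56 lies between the hand values 1.31 and 1.68, and 0.65 lies between 0.79 and 0.58. The direct-effect rows also follow approximately: 1.3 × 1.56 = 2.03 (simulated 1.99) and 0.7 × 1.56 = 1.09 (simulated 1.09).

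**Fallback.** A Cox model stratified by participant type gives each type its own baseline hazard and estimates no coefficient for type. If that branch is taken, the first comparison has no estimate at all.

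**The case against.** The strongest objection is that the protocol never says the type and history coefficients will be reported as the answers to the first and third comparisons. The text describes a serostatus comparison with sensible adjusters, and a statistical analysis plan that is not shown could hold further models. That is fair: a reader might infer that one model is declared for all three contrasts, but this follows only from the absence of any other model under objective 5. What stands is that the protocol fixes this model and its covariates under an objective listing three comparisons, and that as written it is the only source for two of them.

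Secondly, the objective does not use the words total effect, and mutually adjusted associations are a legitimate target in a cohort. However, it asks about risk between residents and staff without reference to antibody status, and it marks only the home's vaccination degree as an adjustment.

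Thirdly, a reader might infer that real differences will disappear and be reported as a hazard ratio of 1.00. The documents do not support that. It requires the whole effect to run through serostatus and serostatus to be measured without error. Exposure, age, testing frequency and immunity that a binary rapid test does not show can all act outside it, and with the protocol's own test accuracy the removal is incomplete.

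Lastly, objective 8 has a staff-resident hazard model without serostatus. It is not a substitute: it runs only if enough non-vaccinated participants are available, it combines them with the vaccinated, it adjusts for prior infection, and it may be restricted to staff.

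**Conclusion.** The point holds as a mismatch between objective and model. Read from the planned model, the resident-staff and prior-infection coefficients are effects not passing through measured serostatus. Whether they are attenuated, shifted or reversed relative to the overall hazard ratios depends on how far serostatus differs between the groups, how strongly it protects, how much of the effect bypasses it, and how accurately it is measured.

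None of these except test accuracy is in the documents, so the size cannot be derived. The simulated results run from a change of little consequence, when seroreversion is nearly equal, through loss of the contrast under full mediation, to a reversal of direction (1.09 to 0.70) when a direct effect opposes the antibody route. If nearly all vaccinated participants stay seropositive in both groups, the distortion is small. The loss of the resident-staff coefficient under the non-proportional-hazards fallback needs no assumption. The planned model remains appropriate for the serostatus contrast.

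**What to change.** - Keep the planned model for the serostatus contrast.
- Estimate the resident-staff and prior-infection hazard ratios among vaccinated participants from a second Cox model that omits post-vaccination serostatus and keeps the nursing-home strata and the time-varying vaccination degree of the home.
- State that the serostatus-adjusted coefficients for type and history are not the answers to those two comparisons.
- State how the resident-staff contrast will be obtained if proportional hazards fail, for example as hazard ratios by period of follow-up. This may matter in the second model too: in the hand check the overall ratio drifts from 1.31 to 1.68 as serostatus diverges, so a single ratio is an average over follow-up.

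The cost is one more model and one more set of estimates to report. No new data are needed.
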